### Outcome ascertainment

During follow-up, incident diagnoses of invasive breast cancer will be identified using the International Classification of Diseases (ICD) version 10 Australian Modification^40^ for the Australian cohorts and the ICD-10^41^ for the Rotterdam Study. ICD-10 code C50.x (malignant neoplasm of breast) will be used to identify invasive breast cancer diagnosis across cancer registries and hospital admission data. In situ breast cancer (eg, D05.x) will not be included in the outcome because hyperplasia and atypical lesions are not precancerous (although some are risk factors), and only some ductal carcinoma in situ are obligate precursors.^42 43^

Cancer registries for all cohorts contain, by statutory requirement, records of all cancers diagnosed or treated and are therefore considered internationally the ‘gold standard’ for cancer identification for research purposes. Since cancer diagnoses for Dutch women and cancer registry data for the Australian women are only currently available until 2016 and 2018 respectively, breast cancers diagnosed later than these dates will be identified from GP data (Dutch women) and hospital data (Australian women). Hospital-derived diagnoses for breast cancer have a positive predictive value and sensitivity of 86% and specificity of 99.9% compared with the cancer registry in the 45 and Up Study population.^44^ Sensitivity analyses showed that 53% of women with a cancer registry diagnosis had an inpatient diagnosis within the same calendar month and 93% within one calendar month; thus, estimations of date of diagnosis align well with Cancer Registry dates.

The date of breast cancer diagnosis used in the study will be the date of diagnosis recorded in either the Australian Cancer Registry or the Rotterdam Study, or the date of the first hospital admission with a principal diagnosis of breast cancer/date recorded in the GP data where registry/study data are unavailable.

### Covariates

A wide range of sociodemographic, lifestyle and clinical potential confounders that may impact prescribing decisions for AHT medicines, a participant’s decision to take prescribed AHT medicines or be associated with an increased risk of breast cancer will be included in the analysis.^45^ Variables will include the following captured at baseline: age, marital status, highest qualification, socioeconomic disadvantage, remoteness, BMI, diabetes, heart disease, stroke, diagnosis of other cancer, comorbidity risk score, number of children and history of hysterectomy/both ovaries removed. In addition, the following time-varying factors (updated annually throughout follow-up and at exit) will be included: statin use, use of combined hormonal contraception, use of combined hormonal replacement therapy. Confounding by comorbidity will be assessed at baseline and also as a time-varying covariate as per the Rx-Risk score (with 5 years look back) that includes 46 clinical conditions based on ATC codes from prescribed medicine claims data, excluding AHT drugs as these medicines are captured in the exposure.^46^ For the secondary aim (cohort-specific analyses), additional covariates will be available depending on the cohort; for example, for the 45 and Up Study cohort, mammographic screening information will be used to differentiate screen-detected cancers; in the ALSWH and Rotterdam cohorts, multiple waves of self-reported/clinical examination data will be used to update lifestyle information during follow-up. In addition, where possible, we will explore the use of earlier study entry to provide longer follow-up. For both Australian cohorts hospital admissions, all specialist services, and GPs visits will be used as time-varying covariates to account for changing propensity to interact with health services. Differences between the cohort-specific analysis and the harmonised analysis undertaken for each cohort will be evaluated to aid with determination of the influence of cohort-specific variables on the association.

Details of the relevant codes (MBS item numbers (Australian women), ATC codes and ICD codes) used to identify participants’ medical conditions, prescribed medicines and health service use from MBS, PBS/pharmacy data, hospital admission, GP data, cancer registries and mortality data collections are provided in online supplemental appendix table 2. A description of data items, questions and response categories from the baseline surveys of the ALSWH and the 45 and Up Study is presented in Online supplemental appendix table 3.

10.1136/bmjopen-2023-080982.supp2Supplementary data

10.1136/bmjopen-2023-080982.supp3Supplementary data

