**Methods and analysis:**

The study will use data from 2 of Australia’s largest cohort studies; the Australian Longitudinal Study on Women’s Health, and the 45 and Up Study, combined with the Rotterdam Study. Eligible women will be those with diagnosed hypertension, no history of breast cancer and no prior CCB use at start of follow-up (2004–2009). Cumulative dose-duration exposure to CCB and other AHT medicines will be captured at the earliest date of: the outcome (a diagnosis of invasive breast cancer); a competing risk event (eg, bilateral mastectomy without a diagnosis of breast cancer, death prior to any diagnosis of breast cancer) or end of follow-up (censoring event). Fine and Gray competing risks regression will be used to assess the association between CCB use and development of breast cancer using a generalised propensity score to adjust for baseline covariates. Time-varying covariates related to interaction with health services will also be included in the model. Data will be harmonised across cohorts to achieve identical protocols and a two-step random effects individual patient-level meta-analysis will be used.

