Participants will be followed until the earliest date of one of the following: the outcome (a diagnosis of invasive breast cancer); a competing risk event (evidence of bilateral mastectomy without a diagnosis of breast cancer, death prior to any diagnosis of breast cancer) or end of the study follow-up (censoring event), whichever came first. Note that since the duration of the available data differs across the longitudinal cohorts, end of study follow-up will be established for each person based on the data available. Figure 1 presents a schematic diagram of timeline for entry, exposure and study exit (ie, recording of the outcome, censoring, competing event or end of follow-up) of our study population.

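### Health-service contacts in the Australian cohort-specific models have no counting window ending before diagnosis, so they can absorb the cancer work-up and bias the CCB estimate in either direction

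*Protocol article*

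**What the plan says.** The Covariates section of the protocol article introduces extra variables for the second aim: "For the secondary aim (cohort-specific analyses), additional covariates will be available depending on the cohort". It then says "For both Australian cohorts hospital admissions, all specialist services, and GPs visits will be used as time-varying covariates", with the purpose "to account for changing propensity to interact with health services". Table 2 agrees on scope. Hospital admissions, specialist attendances and GP attendances are marked as not harmonisable, because Rotterdam has no such data, and they carry no asterisk for the harmonised analysis.

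The abstract is wider. After describing the Fine and Gray model it says "Time-varying covariates related to interaction with health services will also be included in the model", with no limit to the cohort-specific analyses.

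Other relevant statements:

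- **Adjustment.** The Statistical analysis section handles time-varying covariates by ordinary covariate adjustment.
- **Update rule.** For statins and hormonal medicines, "the following time-varying factors (updated annually throughout follow-up and at exit) will be included". No rule is given for contacts.
- **Exit.** Under Study population, follow-up of a case ends at diagnosis.
- **Outcome date.** Where registry data are unavailable (for Australian women, after 2018), the diagnosis date is "the date of the first hospital admission with a principal diagnosis of breast cancer".
- **Lag.** The only lag, under Sensitivity analyses, runs from start of follow-up to outcome and is there for latency.

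**The concern.** The contact covariates are meant to capture how readily a woman uses care. A woman who is about to be diagnosed sees a GP about a symptom, is referred, and may be admitted for diagnosis. These contacts are caused by the cancer. If the counting window runs up to the diagnosis, they enter the covariate as though they were general care-seeking. After 2018, when an admission can itself date the outcome, the admission covariate may contain the event it is used to predict.

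The contact term then takes on a large coefficient that does not reflect risk. If CCB users differ from other women in routine contacts, part of that coefficient is offset through the CCB term. This matters for interpretation because the Covariates section plans to compare each cohort-specific result with the harmonised one, to judge the influence of the added variables. A shift produced by work-up contacts would look like confounding by health-service use, and a real association could be explained away or exaggerated.

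**Working it through.** **No figure to reproduce.** The article gives no estimate of this bias. Its only effect-size figure, ±0.2 under Sample size calculation, has no stated scale and rests on Figure 3, which is not shown. A hazard ratio (HR) of 1.2 is used below as an illustration only.

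**Step 1: can the work-up enter the count?** Contacts are time-varying, all specialist services are included, cases exit at diagnosis, and nothing ends the window earlier. For timing, Outcome ascertainment reports that "53% of women with a cancer registry diagnosis had an inpatient diagnosis within the same calendar month", and 93% within one calendar month. Inpatient breast cancer records therefore cluster around the registry date. These figures do not say which admissions came before the diagnosis, so they show proximity and not the share that would be counted.

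**Step 2: closed form.** Let contacts in the risk set be normal with SD s and mean higher by d in CCB users, and let cases have w extra work-up contacts. The log ratio of the case to non-case contact densities is w(C − m − dX)/s² − w²/(2s²), where C is contacts, X is CCB use and m is the mean in non-users. The coefficient of X is then

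adjusted log HR = true log HR − w·d/s².

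With true HR 1.2 and s = 8 (s² = 64):

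- w = 4, d = 2: 1.2 × exp(−8/64) = 1.06
- w = 6, d = 2: 1.2 × exp(−12/64) = 0.995
- w = 4, d = 0: 1.20
- w = 4, d = −1: 1.2 × exp(4/64) = 1.28

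The sign of the bias is the opposite of the sign of d.

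**Step 3: simulation with skewed counts.** A case versus risk-set logistic model was run with 60,000 cases and 300,000 controls. One-sixth were exposed, from the article's 5:1 ratio. Contacts were negative binomial with mean 10 and shape 2.5 in non-users, giving variance 10 + 10²/2.5 = 50. The mean was multiplied by a contact ratio in CCB users, and cases received Poisson(w) extra contacts. Apart from the 5:1 ratio, every input is an assumption. Estimated HR for a true HR of 1.2, contacts entered linearly:

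| CCB contact ratio | w = 0 | w = 2 | w = 4 | w = 6 |
|---|---|---|---|---|
| 0.8 | 1.20 | 1.29 | 1.41 | 1.55 |
| 1.0 | 1.18 | 1.21 | 1.21 | 1.18 |
| 1.1 | 1.20 | 1.17 | 1.10 | 1.09 |
| 1.3 | 1.18 | 1.06 | 0.98 | 0.87 |
| 1.5 | 1.22 | 1.03 | 0.87 | 0.73 |

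The w = 0 column shows simulation noise of about ±0.02. It also shows that removing the work-up contacts recovers the true value. For a true HR of 1.5 at ratio 1.3, the estimates for w = 2, 4 and 6 are 1.34, 1.24 and 1.08.

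Entering log(1 + contacts) gives the same pattern: 1.135, 1.113 and 1.064 at ratio 1.1, and 1.086, 0.937 and 0.853 at ratio 1.3.

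**Step 4: link to the closed form.** At ratio 1.1 (d = 1) with w = 4 and s² = 50, the formula gives 1.2 × exp(−4/50) = 1.11, against 1.10 simulated.

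**The case against.** The strongest reply is that the fault is read from silence. The article never says that contacts are counted up to diagnosis, and a counting window is the kind of detail an analysis plan may hold. This stands in part: the window is unstated and may be settled elsewhere. But the article does fix the variables, their purpose, the inclusion of all specialist services and the method of adjustment. Followed as stated, that analysis admits the work-up.

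A reader might infer that contacts are updated at exit like the other time-varying factors. The text ties that rule to statins and hormonal medicines only, so the inference is not supported.

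A reader might also infer that the bias must run downwards because CCB users need regular prescriptions. The comparators include users of other antihypertensives, who need them too, and the main Australian analysis requires at least one dispensation in nearly every year from 2003 to 2012. The model also adjusts for other antihypertensive exposure, statins and comorbidity score. The documents give neither the sign nor the size of the remaining CCB–contact difference, so the objection on direction stands.

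It is also fair that the harmonised estimate, without these contacts, will sit beside the adjusted one, so an association could not disappear unseen. What remains is the risk of misreading the difference between the two.

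Finally, the simulation uses a binary exposure. The plan uses cumulative dose, duration and their interaction in a Fine and Gray model with a generalised propensity score. The figures show mechanism and plausible scale, and do not forecast this study's bias.

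**Conclusion.** The concern holds for the Australian cohort-specific analyses. As stated, the contact covariates can include the diagnostic work-up and, where hospital data date the outcome, the outcome admission. The CCB estimate is biased if contacts differ by CCB use, with the direction set by that difference.

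Under the assumed inputs, the bias on a true HR of 1.2 ranges from small (1.17, with 10% more contacts and 2 work-up contacts) to enough to remove or reverse the association (0.98 and 0.87, with 30% more contacts and 4 or 6 work-up contacts). It is upward if CCB users have fewer contacts and absent if contacts are equal.

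A reader of the abstract might conclude that the pooled primary estimate is affected. The Covariates section and Table 2 do not support that, since they keep these variables out of the harmonised analysis. The abstract's unrestricted sentence conflicts with them and needs reconciling.

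The argument does not extend to statins or hormonal medicines, because a breast cancer work-up does not generate those dispensings.

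**What to change.** In the Covariates section:

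- Count GP, specialist and hospital contacts at each time t over a fixed window that ends some months before t, defined identically for cases and for everyone else at risk. Use the look-back data for the first part of follow-up.
- State that contacts are not updated at exit, and exclude admissions with a breast diagnosis.
- Report each Australian cohort-specific estimate with and without the contact covariates, so that their influence is not confused with that of the other added variables.
- Vary the length of the lag in a sensitivity analysis.

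Reconcile the abstract with the Covariates section and Table 2, saying in both places which analyses contain these covariates.

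The cost is some wording, a date shift in the code and slightly older contact information. The article already describes administrative data before entry, so no new data source is needed.

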### Statistical analysis

*Primary aim:* for the primary aim, analysis of the association between CCB use and the development of breast cancer will be undertaken using Fine and Gray competing risks regression with incident breast cancer as the principal event, and death (from causes other than breast cancer) or bilateral mastectomy as the competing risk.^47^ In this setting, the appropriate estimate of the probability of breast cancer is described by the cumulative incidence function rather than an HR. The models will account for confounding factors at entry using propensity scores to balance these factors across exposure status captured over the follow-up period. In addition, we will use standard covariate adjustment for time-varying covariates and any covariates that cannot be balanced using the propensity score. Any significant shifts in practice will be identified via the literature (and our clinical collaborators) and included as categorical variables in the models where appropriate.

Since the CCB exposure variable will be continuous rather than binary a generalisation of the binary propensity score, the generalised propensity score (GPS) developed by Hirano and Imbens will be used.^48^ Since CCB exposure will be sporadic, we will also evaluate the dose-duration response effect by further extending the multivariable models to incorporate a time-dependent dose–response component.^49^ Specifically, the dose-duration response function will be estimated after adjusting for covariate imbalance by using the GPS methods applied in previous publications.^49–52^ The non-linear predictive relationships between the dose duration of CCB exposure and breast cancer will be modelled using non-linear threshold models developed by Gannon *et al*.^53^ Threshold models allow for the differential effect of the dose duration of CCB exposure on the incidence of breast cancer with respect to an individual’s duration and cumulative exposure to CCBs. The model will allow the coefficient (β) to vary according to the days/months/years per unit of the cumulative dose duration while assuming that other components in the model are constant across all individuals to identify the thresholds for subpopulations.^54^ The estimation of the threshold models involves searching all possible values of the dose-duration function with maximum likelihood estimators computed for every tried value. For practical purposes, the number of subpopulations will be limited to 3 or less.^54^ The threshold model that minimises the Bayesian information criterion used for selection of the non-linear models will be the final model. The counterfactual, individuals with no CCB exposure, will also be analysed as a baseline to show the impact of no versus any treatment using standard binary propensity score matching of those exposed versus non-exposed.^51^

*Secondary aim:* for the secondary aim, we will explore relationships between dose duration of CCB use and incident breast cancer and factors that confound and modify these relationships. Using multilevel modelling techniques and time-varying covariates, we will quantify the contributions of person-related, temporal-related and geospatial level-related factors to variation in the dose-duration effect. This will allow the development of both intercountry-specific and intracountry-specific profiles of women who are at higher and lower risk of CCB-attributable breast cancer.

Analyses will be adjusted for multiple comparisons where appropriate. Where the sample size is insufficient to confirm the nature of the association, the results will be regarded as exploratory. Analyses will use Stata SE V.15.^55^ The analysis is scheduled to commence in February 2024 and conclude in July 2025.

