### Data sources

We will use data from the Australian Longitudinal Study on Women’s Health (ALSWH),^27^ the New South Wales (NSW) Sax Institute’s 45 and Up Study (45 and Up Study)^28^ and the Rotterdam Study.^29^

The ALSWH^27^ is a national study that began in 1996 with a random sample of more than 40 000 women in 3 birth cohorts. The surveys were conducted every 3 years since 1996; however, the 1921–1926 cohort was surveyed 6 monthly from November 2011 for health and lifestyle changes. In our study, we will use two longitudinal cohorts, the 1946–1951 cohort (aged 45–50 years at recruitment) and the 1921–1926 cohort (aged 70–75 years at recruitment).Administrative data for the ALSWH are included for all Australian states and territories, linked using probabilistic linkage with clerical review by the data linkage units in each state. Linked data used for this study include hospital admissions, emergency department presentations, cancer registry and the national death index data. Hospitalisation and cancer registry data are recorded separately in each Australian state; hence, the start and end of these datasets vary according to the availability of the data in each state. Medicare Benefits Schedule (MBS) claims and Pharmaceutical Benefits Scheme (PBS) data were provided by Services Australia.The 45 and Up Study^28^ is a longitudinal cohort of 267 357 participants aged ≥45 years residing in NSW, Australia at recruitment randomly sampled from the Services Australia Medicare enrolment database. Participants from rural and remote areas and those 80+ years of age were oversampled. Participants were recruited from 2005 to 2009 (2005 being a pilot study) and followed up every 5 years for changes in health and lifestyle. The response fraction was approximately 19%. Only female participants (53.6% of the cohort) recruited in the main study between 2006 and 2009 will be included in the proposed study.Survey data for the 45 and Up Study were linked to the NSW Admitted Patient Data Collection and the Australian Capital Territory (ACT) Admitted Patient Collection, the NSW and ACT Emergency Department Data Collection, the NSW and ACT Cancer Registry, the NSW and ACT Registry of Births Deaths & Marriages death registrations, the Australian Coordinating Registry Cause of Death Unit Record File, NSW and ACT BreastScreen and the NSW Pap Test Registry by the Centre for Health Record Linkage using a probabilistic linkage procedure with clerical review. The current estimated rate of false-positive linkages is 0.5% (www.cherel.org.au). Linkage of 45 and Up Study cohort data to Medicare claims and PBS data provided by Services Australia was facilitated by the Sax Institute using a unique identifier and deterministic matching.The Rotterdam Study^29^ is a prospective cohort study of persons aged ≥45 years living in the city of Rotterdam, The Netherlands. The study started with a pilot phase in the second half of 1989, called ‘RS-I’. A second cohort was recruited in 2000 (RS-II) and a third cohort in 2006 (RS-III). By the end of 2008, the Rotterdam Study comprised 14 926 participants aged 45 years or over. At baseline, participants were interviewed and had a clinical examination that was repeated every 3–4 years. Follow-up of participants between clinical examinations is undertaken via automated coupling of the study database with medical records from general practitioners (GPs), who receive all relevant medical information from all caregivers of their patients. The data include hospital and specialist discharge summaries providing dates of diagnoses and major surgical interventions. Only female participants of the three longitudinal cohorts will be included in our study.The three Rotterdam longitudinal cohorts are linked at the individual level to records for dispensed medicines from all pharmacies in the study area (1991–2018), the Netherlands Comprehensive Cancer Organisation (1989–2016) and municipality (death) records (1989–2023).

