### Exposure ascertainment

The exposure in this study, for both the primary and secondary aims, will be CCB dispensing including both combination and monotherapy products. Exploring the impact of confounding by indication for non-CCB AHT medicines is important because a modest increased risk of cancer in individuals with hypertension has been documented.^33^ To avoid this issue, previous studies have used a comparator group of patients exposed to other AHTs and/or with a hypertension diagnosis.^34^ Our study population is defined by the presence of hypertension since comparing only to a reference AHT medicine group risks biasing towards the null, if the comparator drug is associated with the outcome. Thus, to reduce bias to the null, women who are both AHT and CCB naïve will be included in the study as long as they meet the entry criteria of hypertension at baseline as described previously. To ensure that exposure to other AHT medicines is accounted for, the cumulative dose-duration exposure of other prescribed AHT medicines (combined) will be captured in the same way as that described for CCB exposure. Thus, in our study, the following four exposure states will be possible during follow-up: (1) women with no exposure to either CCBs or other AHTs; (2) women exposed to other AHTs but not exposed to CCBs; (3) women exposed to CCBs but not exposed to other AHTs and (4) women exposed (at any time) to both CCBs and AHTs. To compensate for immortal-time bias, and to be able to capture the dose–response nature of the association of CCB exposure with risk of breast cancer, a time-varying continuous ascertainment of cumulative exposure (dose duration) to CCB (and separately other AHTs) will be captured as follows.^35^

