For all longitudinal cohorts, the total cumulative duration exposed and the total cumulative dose of each AHT drug class will be calculated from the medicine records available from entry to exit of the study. For all cohorts, the data include information on the date of dispensing, quantity dispensed and the strength of the medicine (derived from the PBS item code for Australian data). In the Rotterdam data, the daily prescribed dose and prescribed duration of use are also available.^29^ This information is not present in the Australian data necessitating estimation of the duration of the medicine. For the Australian data, the reverse waiting time distribution method with multiple random index dates will be used to determine the following: (1) the median duration of medicine possession, defined as the number of days that 50% of prevalent users of the same medicine refill their scripts and (2) the upper duration limit of medicine possession, defined as the number of days that 80% of prevalent users of the same medicine refill their scripts.^37 38^ The median duration will be used as the usual possession duration of the medicine in calculating the total duration (days) of medicine possession in contiguous periods of exposure. The contiguous period will be defined as a series of dispensings of the same AHT class with no break between dispensing that is greater than the upper duration limit of medicine possession of the last medicine in the series. The total cumulative duration (days) of exposure to each AHT class under investigation for each individual over the study period will be the sum of the number of days accrued over all contiguous periods of exposure. The total cumulative dose will be similarly captured across all contiguous periods of exposure by summing the total milligrams (mg) of medicine dispensed of all dispensations (strength/unit multiplied by total units dispensed).

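### Fine and Gray regression does not suit a time-updated cumulative CCB exposure: the primary estimate is biased under the null, in a direction and size that depend on how exposure is entered

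*Protocol article*

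**What the plan says.** The Statistical analysis section (primary aim) says that "analysis of the association between CCB use and the development of breast cancer will be undertaken using Fine and Gray competing risks regression". The competing events are death from other causes and bilateral mastectomy. It adds: "In this setting, the appropriate estimate of the probability of breast cancer is described by the cumulative incidence function rather than an HR". The article names no cause-specific hazard model.

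Exposure ascertainment calls for "a time-varying continuous ascertainment of cumulative exposure (dose duration) to CCB (and separately other AHTs) will be captured as follows", in order to deal with immortal-time bias. Totals for each drug class are "calculated from the medicine records available from entry to exit of the study", and Study population makes death one of the exits. Prior CCB users are excluded, so every woman starts at zero. Statistical analysis then speaks of "extending the multivariable models to incorporate a time-dependent dose–response component".

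Other wording points elsewhere. The Abstract has cumulative dose-duration captured at the date of outcome, competing event or end of follow-up. Exposure ascertainment measures time since last CCB use backwards from exit. Both can be read as one value per woman, taken at exit.

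**The concern.** A subdistribution risk set keeps women after a competing event. CCB dose-duration is an internal covariate: it has no value after death and can accrue only while a woman lives. At any later time the risk set mixes living women, whose exposure is still rising, with dead women, whose exposure stopped at death. Breast cancers arise only among the living. Cases therefore tend to show more exposure than the risk-set average when there is no effect at all. The generalised propensity score balances covariates at entry and cannot touch this, because the bias arises without any confounding.

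The study asks whether CCB use raises the rate of breast cancer and whether there is a dose–response. A bias that moves with survived exposure time can look like a dose–response. A bias that depends on mortality and on cohort-specific eligibility can look like a difference between cohorts or countries, which is the secondary aim. A cumulative incidence function also cannot be predicted from a covariate that ceases to exist at death.

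**Working it through.** **The plan's own figure.** Sample size calculation claims 80% power at 95% confidence for an effect of ±0.2 with 5:1 unexposed to exposed. It cannot be reproduced: the exposed counts are in Figure 3 (not shown) and the scale of ±0.2 is not given. Nothing below depends on it.

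**Inputs.** From the article: zero exposure at entry, accrual ending at exit, death as a competing event, follow-up of up to 19 years (Discussion). Assumed, because the article gives none: mortality μ, CCB initiation λ = 2–5% a year, follow-up T = 12 years, rare outcome, no CCB effect on cancer or death, common administrative censoring, last exposure value kept after death.

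**Step 1: expected score under the null, ever use.**

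- Surviving share: S(t) = exp(−μt).
- Ever-users among the living: a(t) = 1 − exp(−λt).
- Ever-users in the subdistribution risk set: P(t) = 1 − [exp(−(μ+λ)t) + μ/(μ+λ) × (1 − exp(−(μ+λ)t))].
- The null ratio θ solves ∫₀ᵀ S(t) {a(t) − θP(t)/(1 − P(t) + θP(t))} dt = 0.

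Example, μ = 0.04, λ = 0.05, t = 12: a = 1 − exp(−0.60) = 0.451; P = 1 − [0.340 + 0.444 × 0.660] = 0.367. Of potential cases 45% are ever-users, against 37% of the set they are compared with.

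| Mortality per year | Null ratio, 12 years (λ 2–5%) |
|---|---|
| 0% | 1.00 |
| 1% | 1.045–1.052 |
| 2% | 1.09–1.10 |
| 4% | 1.18–1.20 |
| 8% | 1.34–1.38 |

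At 16 years, 4% gives 1.24–1.28 and 8% gives 1.45–1.51.

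**Step 2: simulation on null data.** 400,000 women per scenario, 12 years, assumed CCB start 5%, stop 10% and restart 10% a year, breast cancer 0.4% a year. Ratios per year of cumulative use (95% CI):

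| Mortality | Fine and Gray | Cause-specific Cox |
|---|---|---|
| 0% | 0.999 (0.992–1.007) | 0.999 |
| 2% | 1.026 (1.018–1.035) | 0.998 |
| 4% | 1.052 (1.042–1.062) | 0.997 |
| 8% | 1.106 (1.094–1.118) | 0.999 |

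Over five years of use: 1.026⁵ = 1.14, 1.052⁵ = 1.29, 1.106⁵ = 1.65. With 20,000 women and 200 replicates, Fine and Gray rejected the true null for cumulative duration in 13.5%, 28.5%, 62.5% and 94.5% of runs at 1%, 2%, 4% and 8% mortality. Cause-specific Cox rejected in 3–6%.

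**Step 3: the concession rule.** Study population and Sensitivity analyses require Australian women to show concessional dispensing in each year from 2003 to 2012, with one year allowed missing. Read literally, a woman who died in 2010 lacks both 2011 and 2012 and is excluded. No retained woman then dies before 2011, which is 2 to 7 years after entry in 2009 to 2004. Setting μ = 0 for the first 3, 5 or 7 years in Step 1:

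| Mortality afterwards, follow-up | 3 years | 5 years | 7 years |
|---|---|---|---|
| 2%, 12 years | 1.04 | 1.02 | 1.01 |
| 8%, 12 years | 1.12 | 1.05 | 1.02 |
| 8%, 16 years | 1.19–1.21 | 1.11 | 1.06 |

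Rotterdam has no such rule. With the same 8% mortality over 12 years it would show 1.34–1.38 where the Australian cohorts show 1.02–1.12, although no effect exists in either.

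**Step 4: other modifiers.** Adding cumulative exposure to other antihypertensives, which the plan intends, lowered the ever-use ratio from 1.37 to 1.22 at 8% mortality and from 1.19 to 1.14 at 4%. This is a single run, assuming 70% on such drugs at entry. If current CCB use raises death threefold (mortality 3%), the ever-use ratio is 0.96 (0.92–1.00), while the per-year ratio stays at 1.019 (1.009–1.030).

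**Step 5: exit total as a fixed covariate.** On the Step 2 data the Fine and Gray ratio per year of use is 0.82 at 0% mortality and 0.88 at 8%. The bias is there even with no deaths: a woman diagnosed early has had less time to accrue, and later exposure is credited backwards. On this reading a change of regression model alone would not help.

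**The case against.** A reader might infer that the plan is bound to produce a false harmful association, as large as the effect the study seeks and worst in the 1921–1926 cohort, aged about 78 to 87 at entry, and in the 45 and Up Study, where "those 80+ years of age were oversampled". The article does not support that.

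- **Direction.** Carrying the last value forward is inferred from accrual ending at exit. The exit-total reading reverses the sign, and the time-dependent component is worded as an extension of the models. Much faster death among CCB users could remove the bias for ever use.
- **Size.** Neither mortality nor CCB initiation is given. The ±0.2 has no scale; even if it meant a ratio of 1.2, the bias reaches that only at about 4% mortality, with deaths from the first day and no other-antihypertensive term.
- **Cohort.** The older Australian women fall under the concession rule, which read literally removes early deaths and most of the bias. That rule raises its own problem, which is separate from this one.

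These points stand. It can also be said that covariate handling after death belongs in an analysis plan that is not shown. That does not remove the point. The article fixes both the regression model and a time-updated exposure, and any post-death value an analysis plan assigned would have to be invented.

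**Conclusion.** The primary model is a poor match for the stated exposure, and neither available reading gives a valid estimate under the null. With time-updated exposure and last value carried forward, the bias is usually upward and grows with mortality: an ever-use ratio of about 1.05 at 1% up to about 1.35 at 8%, over 12 years with 2–5% annual initiation. It is about 1.02–1.12 at 8% where the concession rule removes early deaths, smaller again with other antihypertensives in the model, and possibly absent for ever use if CCB users die much faster. With the exit total as a fixed covariate the bias is downward, about 0.82–0.88 per year of use.

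All sizes rest on assumed rates and illustrate a range; they do not predict this study's result. What rests on the article itself is the conflict between model and exposure, the inability of baseline adjustment to cure it, and its scope to differ between cohorts.

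**What to change.** 1. Reconcile the Abstract, Exposure ascertainment and Statistical analysis so that CCB and other antihypertensive exposure, and time since last use, are defined as updated up to each event time, not as one value at exit.
2. Make a cause-specific Cox model with that exposure the primary association model in every cohort and the source of the pooled estimates, treating death and bilateral mastectomy as censoring events. On the null data above it stayed at 0.997–1.003 per year of use.
3. Keep Fine and Gray and cumulative incidence for describing absolute risk, with exposure fixed at baseline or at a landmark (for example, use in the first 5 years among women event-free at 5 years).

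Both parts are needed: the Cox model does not rescue an exit total, and updating exposure does not rescue Fine and Gray. The cost is a change of wording, with the same data and standard software. The downside is that absolute risks come from a separate secondary analysis.
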